**V.Feeding Practices**

***Past***

1. When was breastfeeding initiated after birth?

1.Within 1 hour 2. 1-4 hours 3.4-24 hours 4.After 24 hours 5.Not Given

1. Which food was given first after birth (Pre lacteal feed)?

1.Breast milk 2.Animal milk 3.Standard formula 4.Ghutti 5..Honey 6.Others

1. Did you feed colostrum to the child? 1.Yes 2.No
2. Did your baby receive exclusive breastfeeding (EBF) till 6 months of age? 1.Yes 2.No 3.Baby <6 months of age but on EBF 4.Baby < 6 months but not EBF
3. If No, reason 1.Decreased milk secretion after birth 2. Mother not feeling well/ tired 3.Working mother 4.Baby not satisfied/hungry 5. Prelacteal feed
4. Did your baby receive bottle feeding at any time before 6 months of age? 1.Yes 2. No

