***Formative research***

Focus group discussions (FGDs)will be conducted separately with each group of mothers, ANMs, AWWs and community representatives to explore the culturally appropriate foods for infants, gap between knowledge and action of mothers, frequency of infant feeding, feeding practices etc, using FGD guide, till data saturation (Annexure 1). Result of the FGDs will help in the modifying the nutritional education intervention as per the need of mothers and health workers, and development of child undernutrition tracking module for monitoring and supervision of child growth by health workers. Pilot testing of the intervention will be conducted in an area similar to the study area but not in study area.

1. **Baseline Assessment**

Baseline assessment of maternal knowledge of infant feeding, infant feeding practices by 24 hour dietary recall (frequency of feeding, number of meals and snacks per day) and hand hygiene practices will be done by using a pretested semi-structured questionnaire (Annexure 2). Feeding on the day before the interview will be used to represent the infant feeding practices. The status of under-nutrition will be assessed by baseline anthropometry of the infants by using Digital Salter Model 235, CMS weighing equipment and stadiometer (SECA height board UNICEF) for measuring weight for age, weight for length and length for age [59,60]. The knowledge of ANM and *anganwadi* workers on infant feeding and status of growth monitoring will be checked by a pre tested semi-structured questionnaire (Annexure 3). It will be assessed in both study and intervention arm.

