**4. Post-intervention phase**

End line assessment of maternal knowledge of infant feeding and infant feeding practices, 24 hour dietary recall (consuming foods from 4 or more food groups, recommended number of meals and snacks per day) will be done by using the same pretested semi-structured questionnaire as was used in baseline assessment in study and control area (Annexure 2). The status of undernutrition will be assessed by anthropometry of the infant (wt/age, wt/length, length/age). Similarly, the knowledge of ANMs and *anganwadi* workers on infant feeding and status of growth monitoring will be checked by the same pretested semi-structured questionnaire (Annexure 3) in both intervention and control arm.

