**Secondary outcome:**

- Mean change in the weight for height.
- Mean change in the Height for age.
- Change in level of maternal knowledge and practice of recommended infant and child feeding practice following intervention.
- Change in proportion of infants who were consuming foods from four or more food groups
- Change in proportion of infants who were consuming the recommended number of meals and snacks per day

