***Current***

1. What is the current feeding practice?

1.Only breastfeeding 2.Breast milk + animal milk or formula milk
 3.Breastfeeding+ Complementary feeding 4. Completely weaned

If child below 6 months & answer is option 1 or 2, then skip to question no. 94

1. At what age did you started giving your child solid/semi-solid foods?

1.< 6 months 2. At 6 months 3.7-9 months 4.10 months and above
 5.Not started

1. Type of complementary food being fed to the baby?

1.Cow/Buffalo milk 2.Commercial baby food 3.Homemade semi-solid/solid food 4.Commercial baby food + homemade food 5. Homemade semi-solid/solid food + Cow/Buffalo milk 6. Cow/Buffalo milk + Commercial baby food

7. Homemade semi-solid/solid food + Cow/Buffalo milk + Commercial baby food

1. Is your baby currently receiving bottle feeding? 1.Yes 2. No
2. Is your child eating thick food first at the main meal? 1.Yes 2. No
3. How many times in past 24 hours, your child has taken solid/semi-solid foods? ( 0/ 1 / 2 / 3 / 4 / 5 )
4. What is the quantity of solid/semi-solid foods your child can consume at his/her age per feed?

| - 1. 2-3 tablespoonfuls | - 1. 3-4 tablespoonfuls |
| --- | --- |
| - 1. 4-5 tablespoonfuls | - 1. 2/3^rd^ of a 250 ml cup |
| - 1. 3/4^th^ of a 250 ml cup | - 1. Full cup |
| - 1. Full cup |  |

1. What is the mode of feeding the child? 1.By spoon 2.By hand 3.Both 4.Self by hand/spoon
2. What is consistency of feeds being received by your child? 1.Thick 2.Thin 3.Very thin
3. Are you adding ghee or oil in complementary foods? 1.Yes 2.No
4. Average food group taken daily in last 7 days except milk : 1 / 2 / 3 / 4 / 5

| Food groups | Every day | Weekly thrice | Weekly twice | Never |
| --- | --- | --- | --- | --- |
| **Cereals & Starches, tubers** -Rice, Bread atta, suji, dhaliya, corn flakes, Poha |  |  |  |  |
| Potato, carrot, sweet potato |  |  |  |  |
| **Commercial products** - cerelac, farex |  |  |  |  |
| **Commercial infant formula-** lactogen, nestogen, Nan |  |  |  |  |
| **Pulses- nuts, legumes**,  Any dhal, lentils, Peanuts, Almonds, Cashew nuts , besan, Beans |  |  |  |  |
| **Dairy products:** milk, curds, paneer |  |  |  |  |
| Green leafy vegetables-palak, methi. |  |  |  |  |
| **Other Vegetable and Fruits:** pumpkin, bottle guard, cabbage |  |  |  |  |
| Fruits - banana, apple, papaya, orange |  |  |  |  |
| **Meat/fish/chicken** |  |  |  |  |
| **Egg** |  |  |  |  |
| **Oil/ghee/butter** |  |  |  |  |
| Miscellaneous: Sugar/ jaggary |  |  |  |  |

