| Biscutes |  |  |  |  |
| sawary snacks |  |  |  |  |
| carbonated drinks |  |  |  |  |
| Tea |  |  |  |  |
| Tetra packet juices(Fruity or maza) |  |  |  |  |
| Maggi noodles, macoroni, pasta |  |  |  |  |
| junk food kurrkurr, chips, pizza,burger |  |  |  |  |
| Chocolates or sweets |  |  |  |  |

1. Are you feeding tea/ sugar drinks to your child? 1.Yes 2. no
2. Is your child receiving any snacks in between meals? 1.Yes 2. No
3. Do you wash the child’s hands with soap before feeding? 1.Yes 2.No
4. Do you wash your hands with soap and water before feeding the child? 1.Yes 2. No
5. Do you maintain eye contact and talk to your child while feeding him/her? 1.Yes 2.No
6. Do you encourage your child to take feed by praising him/her?1.Yes 2. No

|  | Item | Quantity | Calories |
| --- | --- | --- | --- |
| Early morning |  |  |  |
| Breakfast |  |  |  |
| Midmorning |  |  |  |
| Lunch |  |  |  |
| Post lunch |  |  |  |
| Evening |  |  |  |
| Dinner |  |  |  |

1. Total Calories Consumed-……………. (1=Deficit 2= Excess)……………
2. CS-ICFI score……………….

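### The per-feed amount question under Current feeding practices repeats the knowledge question and asks what the child can eat, so learned amounts can be counted as changed practice

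*Protocol*

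**What the plan says.** The protocol lists among its secondary outcomes "Change in level of maternal knowledge and practice of recommended infant and child feeding practice following intervention". The end-line assessment (Methodology, Post-intervention phase) "will be done by using the same pretested semi-structured questionnaire as was used in baseline assessment in study and control area", so Annexure 2 supplies both readings. For the reference period, the Baseline Assessment paragraph says: "Feeding on the day before the interview will be used to represent the infant feeding practices".

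Annexure 2 keeps knowledge (section IV) apart from feeding practices (section V), and splits section V into Past and Current. The Current block asks about the amount per feed in these words: "What is the quantity of solid/semi-solid foods your child can consume at his/her age per feed". Section IV asks the same question with the same stem and a partly different list of answers.

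The mothers' training module (Annexure 5, part B) is a table of amounts per meal by age. The control group receives routine health education only (Methodology, Intervention Phase).

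The Past block holds three questions about events around birth: "When was breastfeeding initiated after birth", the first food given, and "Did you feed colostrum to the child".

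**The concern.** The outcome names knowledge and practice separately, and the practice part is meant to show that feeding changed. A question about what a child can take at a given age tests whether the mother knows the recommended amount. Asked under practice, after one area has been taught those amounts, it can show an improvement that is only recall of the lesson. The shift is expected mainly in the study area, so comparing change between areas would not remove it. Answers are self-reported to the investigator in a comparison of two purposively chosen areas, so neither blinding nor randomisation offsets this.

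**Working it through.** The point concerns wording and no stated figure depends on it, so the main check sets the texts side by side.

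**1. Same question in two sections**

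| | Knowledge (Annexure 2, IV) | Practice (Annexure 2, V, Current) |
| --- | --- | --- |
| Stem | "What is the quantity of solid/semi-solid foods your child can consume at his/her age per feed" | identical |
| What it asks | capacity for age | capacity for age |
| Time reference | none | none |

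The neighbouring frequency item in the Current block does ask how often the child ate in the past 24 hours. The amount item has neither a period nor a verb of actual intake, so it does not follow the day-before rule. Some other Current items also lack a reference day, and the food-group item uses seven days, but those still ask what is done. The sharper fault is therefore capacity in place of intake.

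**2. Taught amounts against the practice answer options**

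| Age in the module | Amount taught | Among the practice options? |
| --- | --- | --- |
| from 6 months | 2 to 3 tablespoonfuls | yes |
| 7 to 8 months | up to 2/3 of a 250 ml cup | yes |
| 9 to 11 months | 3/4 of a 250 ml cup | yes |
| 12 to 24 months | full 250 ml cup | yes |

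All four taught amounts can be selected. A mother who remembers the table can pick the entry for her child's age whatever the child ate.

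**3. How much of a practice score this could be (illustration)**

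The protocol gives no scoring rule beyond an undefined CS-ICFI field, so equal weight per item is an assumption. Section V has 6 Past items, of which one only asks the reason for a No, leaving 5. It has 17 Current items. Total 5 + 17 = 22; other ways of counting give 20 to 23.

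- Largest contribution of the amount item, if every mother moved from a wrong to a right answer: 100/22 = 4.5 points (100/23 = 4.3; 100/20 = 5.0).
- Share of the three birth-time items, if they were scored: 3/22 = 13.6% (3/23 = 13.0%; 3/20 = 15.0%). Answered truthfully at both visits they contribute a change of 0, so they would dilute a percentage-score change by that share and not enlarge it.

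**4. Is intake recorded elsewhere?** Yes. The 24-hour grid has a Quantity column for each of seven eating occasions. The counselling checklist in Annexure 4, session 3, already asks about the quantity eaten at the main meal on the previous day. The protocol therefore has suitable wording and a second source.

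**The case against.** The strongest reply is that this is one item. Most Current questions ask about behaviour (frequency in the past 24 hours, consistency, added ghee or oil, snacks, handwashing), the grid records quantities, and the answer lists of the two amount items differ. The item might also be left out when a statistical analysis plan defines the practice measure. All of this limits the size of the problem. It does not repair the wording: no later scoring rule can turn an answer about capacity into a record of intake.

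A reader might go further on three matters. The documents do not support it.

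- **Birth-time items.** One might infer that initiation, first feed and colostrum would manufacture improvement through taught answers. The protocol nowhere says they enter the practice outcome, and it labels them Past. The key messages in the mothers' and health workers' modules do not cover colostrum, early initiation or prelacteal feeds. A changed answer would be recall or desirability error, and the documents give no basis for its frequency.
- **Exclusive breastfeeding.** The item has separate codes for infants under 6 months, which might look like a change of variable. They are valid age categories. Infants enrolled at 4 to 6 months and followed for 6 months all fall under the two completed-status codes at end line.
- **Calories.** The code "1=Deficit 2= Excess" and the lack of a breast-milk row might suggest bias against continued breastfeeding. Energy is not a listed outcome. The form also has a blank for total calories, a calorie column per meal and a free Item field, and the documents give no ground for expecting weaning to differ between the areas.

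**Conclusion.** Wrong as written, and minor. The Current amount item measures knowledge, departs from the protocol's own day-before rule, and offers as answers the amounts taught only in the study area. A change on it between baseline and end line cannot be told apart from learning, and it can favour the intervention arm in the practice part of this secondary outcome.

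The effect is confined to one item, at most about 4 to 5 points in 100 under assumed equal weights. If the item were reported alone, none of its change could be read as changed practice. The primary outcome (weight for age) and the secondary outcomes on food groups and on meals and snacks do not depend on it. It would be too strong to conclude that the practice outcome as a whole consists of taught answers.

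This rests on mothers understanding the question as worded, and on the item being used in the practice outcome, which its place under Current feeding practices implies but no scoring rule confirms.

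**What to change.** In Annexure 2, section V, Current, reword the amount item to ask how much the child actually ate per feed on the day before the interview. Alternatively, derive it from the Quantity column of the 24-hour grid. Keep the can-consume wording in section IV only, as a knowledge item.

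As a small accompanying step, state that initiation of breastfeeding, first feed and colostrum are baseline descriptors and lie outside any measure of change in practice. They need be asked only once.

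The cost is one reworded question and one sentence in the outcome definition. No extra visits, staff or infants are needed. The same wording must be used at baseline and end line in both areas. If baseline interviews have already used the current wording, the grid is the only source comparable at both times.

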***Current***

1. What is the current feeding practice?

1.Only breastfeeding 2.Breast milk + animal milk or formula milk
 3.Breastfeeding+ Complementary feeding 4. Completely weaned

If child below 6 months & answer is option 1 or 2, then skip to question no. 94

1. At what age did you started giving your child solid/semi-solid foods?

1.< 6 months 2. At 6 months 3.7-9 months 4.10 months and above
 5.Not started

1. Type of complementary food being fed to the baby?

1.Cow/Buffalo milk 2.Commercial baby food 3.Homemade semi-solid/solid food 4.Commercial baby food + homemade food 5. Homemade semi-solid/solid food + Cow/Buffalo milk 6. Cow/Buffalo milk + Commercial baby food

7. Homemade semi-solid/solid food + Cow/Buffalo milk + Commercial baby food

1. Is your baby currently receiving bottle feeding? 1.Yes 2. No
2. Is your child eating thick food first at the main meal? 1.Yes 2. No
3. How many times in past 24 hours, your child has taken solid/semi-solid foods? ( 0/ 1 / 2 / 3 / 4 / 5 )
4. What is the quantity of solid/semi-solid foods your child can consume at his/her age per feed?

| - 1. 2-3 tablespoonfuls | - 1. 3-4 tablespoonfuls |
| --- | --- |
| - 1. 4-5 tablespoonfuls | - 1. 2/3^rd^ of a 250 ml cup |
| - 1. 3/4^th^ of a 250 ml cup | - 1. Full cup |
| - 1. Full cup |  |

1. What is the mode of feeding the child? 1.By spoon 2.By hand 3.Both 4.Self by hand/spoon
2. What is consistency of feeds being received by your child? 1.Thick 2.Thin 3.Very thin
3. Are you adding ghee or oil in complementary foods? 1.Yes 2.No
4. Average food group taken daily in last 7 days except milk : 1 / 2 / 3 / 4 / 5

| Food groups | Every day | Weekly thrice | Weekly twice | Never |
| --- | --- | --- | --- | --- |
| **Cereals & Starches, tubers** -Rice, Bread atta, suji, dhaliya, corn flakes, Poha |  |  |  |  |
| Potato, carrot, sweet potato |  |  |  |  |
| **Commercial products** - cerelac, farex |  |  |  |  |
| **Commercial infant formula-** lactogen, nestogen, Nan |  |  |  |  |
| **Pulses- nuts, legumes**,  Any dhal, lentils, Peanuts, Almonds, Cashew nuts , besan, Beans |  |  |  |  |
| **Dairy products:** milk, curds, paneer |  |  |  |  |
| Green leafy vegetables-palak, methi. |  |  |  |  |
| **Other Vegetable and Fruits:** pumpkin, bottle guard, cabbage |  |  |  |  |
| Fruits - banana, apple, papaya, orange |  |  |  |  |
| **Meat/fish/chicken** |  |  |  |  |
| **Egg** |  |  |  |  |
| **Oil/ghee/butter** |  |  |  |  |
| Miscellaneous: Sugar/ jaggary |  |  |  |  |
| Biscutes |  |  |  |  |
| sawary snacks |  |  |  |  |
| carbonated drinks |  |  |  |  |
| Tea |  |  |  |  |
| Tetra packet juices(Fruity or maza) |  |  |  |  |
| Maggi noodles, macoroni, pasta |  |  |  |  |
| junk food kurrkurr, chips, pizza,burger |  |  |  |  |
| Chocolates or sweets |  |  |  |  |

1. Are you feeding tea/ sugar drinks to your child? 1.Yes 2. no
2. Is your child receiving any snacks in between meals? 1.Yes 2. No
3. Do you wash the child’s hands with soap before feeding? 1.Yes 2.No
4. Do you wash your hands with soap and water before feeding the child? 1.Yes 2. No
5. Do you maintain eye contact and talk to your child while feeding him/her? 1.Yes 2.No
6. Do you encourage your child to take feed by praising him/her?1.Yes 2. No

|  | Item | Quantity | Calories |
| --- | --- | --- | --- |
| Early morning |  |  |  |
| Breakfast |  |  |  |
| Midmorning |  |  |  |
| Lunch |  |  |  |
| Post lunch |  |  |  |
| Evening |  |  |  |
| Dinner |  |  |  |

1. Total Calories Consumed-……………. (1=Deficit 2= Excess)……………
2. CS-ICFI score……………….

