**Inclusion criteria**

1. Mother-infant dyad with age of infant between 4 to 6months of age.
2. Parents who are residing in the study area for the past 6 months and have no plans to migrate during the intervention period.
3. Mothers, ANMs and *anganwadi* workers who will give consent to be the part of the study.

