**Data Collection**

Data on anthropometry will be collected at baseline and 6 months of intervention in both study and control group. Data collection will be done by the chief investigator who is a junior resident in the Department of Community Medicine. After data collection, all filled forms will be manually checked for completeness and consistency.

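### The baseline skip in the mothers' questionnaire drops current bottle feeding and tea/sugar drinks, which do not depend on solids, so change in these two practices is not measured like for like

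*Protocol*

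**What the plan says.** Annexure 2, section V, opens its current-feeding part with a four-way question on present practice. The two answers that trigger the skip are "1.Only breastfeeding 2.Breast milk + animal milk or formula milk". The instruction reads "If child below 6 months & answer is option 1 or 2, then skip to question no. 94".

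Further down the same part come "Is your baby currently receiving bottle feeding? 1.Yes 2. No" and "Are you feeding tea/ sugar drinks to your child? 1.Yes 2. no".

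The inclusion criterion is "Mother-infant dyad with age of infant between 4 to 6months of age". On timing, the Data Collection section says "Data on anthropometry will be collected at baseline and 6 months of intervention in both study and control group". The post-intervention section says that endline feeding practice will be recorded with the "same pretested semi-structured questionnaire as was used in baseline assessment in study and control area".

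One of the listed secondary outcomes is "Change in level of maternal knowledge and practice of recommended infant and child feeding practice following intervention".

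**The concern.** A skip in a feeding questionnaire is sensible where the later items presuppose solid food. This one also removes two items that do not. An infant on breast milk plus animal or formula milk may well be fed by bottle, and may be given sweetened drinks, without having started solids. That infant is sent past both questions at baseline and asked both at endline.

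The study is quasi-experimental with two purposively chosen areas, so a baseline is what separates an effect from a difference that was already there. The knowledge section asks every mother, at both visits, whether bottle feeding and tea or sugar drinks are acceptable. The matching practice items have no direct baseline answer in the skipped group. A paired change would rest on the infants who were not skipped. An unpaired change would set that subset at baseline against everyone at endline. If early feeding differs between the areas, the subset can differ between arms as well.

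**Working it through.** **Step 1: locate the skip target.** Item numbers are visible only for items 32 to 45 of Annexure 2, so the rest are counted.

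- Section I has 15 items plus 4 after the code lists (family income, socioeconomic score, socioeconomic class, food security): items 1–19.
- Section II has 12 items up to immunization status: 19 + 12 = 31. BCG should therefore be item 32, which is its printed number. Present weight is printed as 45.
- Remaining anthropometry: 46–50. Housing, 8 items: 51–58. Knowledge, 15 items: 59–73. Past feeding, 6 items: 74–79.
- Current practice, carrying the skip: 80. Current bottle feeding: 83. Food-group grid: 90. Tea/sugar drinks: 91. Snacks: 92. Washing the child's hands: 93. Mother washing her own hands: 94.

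The skip therefore omits items 81–93. A miscount of one or two leaves items 83 and 91 inside the block. Item 93 is less secure because it adjoins the target.

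**Step 2: when the rule can apply.** At entry, infants are 4 to 6 months old, so nearly all are under 6 months. After six months they are at least 4 + 6 = 10 months old, so the age condition fails for everyone and all items are asked.

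**Step 3: what can still be recovered at baseline.**

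| Practice | Other baseline source | What it settles | What stays open |
| --- | --- | --- | --- |
| Current bottle feeding | Item 79, any bottle feeding before 6 months, asked before the skip | No means no current use in an infant still under 6 months | Yes does not show whether use continues |
| Tea/sugar drinks, breastfeeding only | Item 80, first option | As worded, excludes such drinks | Nothing material |
| Tea/sugar drinks, breast milk plus other milk | 24-hour recall grid, printed after item 96 and so past the skip target | May show drinks given the day before | A direct answer to the question asked at endline |

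The recall grid has columns for item, quantity and calories and none for bottle use, so it does not help with the first row. The food-group grid (item 90) has a tea row but lies inside the skipped block.

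**Step 4: size, under assumption.** The Protocol gives no share of infants under 6 months in the first two options. With 202 per arm from the Sample size section, skipped = share × 202:

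| Assumed share skipped | Basis | Skipped per arm | Direct answer per arm |
| --- | --- | --- | --- |
| 44.2% | 1 − 0.558; 55.8% is the Introduction's figure for complementary feeding at 6–9 months | 89 | 113 |
| 77.5% | share starting at six months in the cited 2011 Karnataka study | 157 | 45 |
| 90% | assumption | 182 | 20 |

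None of these figures describes the enrolled population. The first concerns older infants, so the share not yet on solids before 6 months would be expected to be higher. All three treat not being on solids as being skipped, which ignores infants fully weaned or already 6 months old.

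**The case against.** The strongest reply is that much of the baseline is already on the form. Item 79 is put to everyone, and for an infant still under 6 months its period includes the present, so a no is as good as a no to item 83. Breastfeeding alone excludes tea. The Baseline Assessment section plans a 24-hour recall without exempting skipped infants. All of this stands, and it narrows the point.

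A reader might infer that change can be computed only in infants fed solids early. The document does not support that: infants already 6 months old and those completely weaned are not skipped, and some skipped infants have an inferable value. A reader might also take 157 of 202 per arm as having no baseline value. That does not hold either. The count includes infants whose status follows from other items, and the 77.5% comes from a study that the Protocol's own literature table calls hospital based and not representative of the general population.

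It is also fair to say that the secondary outcomes name neither bottle feeding nor tea, that the Statistical Analysis section ties difference in difference to weight, and that omitting the item on the child's hands for an infant fed only at the breast is defensible.

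Inference does not close the gap for infants who also take animal or formula milk. The Protocol gives no rule for deriving these answers from other items, and a one-day recall is a different measurement from the endline question.

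**Conclusion.** The point holds as a minor defect in the order of the questionnaire. At baseline the skip removes two items that do not depend on solids, and at endline the same form asks them of every infant. What cannot be recovered is current bottle use among infants with a yes on the past item, chiefly those on breast milk plus animal or formula milk, and a direct tea/sugar-drink answer in that same feeding group. Change from baseline in these components of the feeding-practice outcome is therefore not like for like.

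Under assumed skipped shares of 44% to 90%, about 89 to 182 of 202 infants per arm would have no direct baseline answer. The number with no usable value after inference is smaller, and the document gives no basis for estimating it. That most infants would be skipped is likely given entry at 4 to 6 months, but it is not documented.

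The endline comparison between arms on these items is complete, though it cannot adjust for a starting difference between the two areas. The primary outcome and the growth outcomes do not use these items.

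**What to change.** Move the current bottle-feeding and tea/sugar-drink items ahead of the skip so that every mother answers both at both visits. Keep the skip for items that need solid food. The item on washing the child's hands could be moved too, but that is optional. The cost is two or three short questions per baseline interview and a renumbered form, with no change to sample size, visits or analysis. If baseline interviews have already been done, state in advance which values will be inferred from the past bottle-feeding item, the feeding option and the recall, and report the rest as missing.
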